### Outcomes and sample size

The primary outcomes of interest will be improvement of a major biomarker of EED, the percent of ingested lactulose excreted in the urine (Δ%L), from baseline to 8 weeks and to 16 weeks. Linear growth has been shown to best correlate with this component of the traditional dual-sugar absorption test [42]. The enrollment goal will be at least 86 subjects in each of two equally sized intervention or control groups. This sample size was chosen to detect a decrease of 0.05% in Δ%L between the two groups (considered to be a clinically significant improvement in gut barrier function) with an alpha value of 5% and 90% power. This assumes that urinary lactulose measurements will be distributed similarly to prior studies that showed that more than 80% of apparently healthy rural Malawian children had EED. Additional children will be enrolled to account for children who drop out or are excluded during the course of the study, as well as for some children who will not have a satisfactory data collection due to technical issues with the urine collection. The differences in lactulose recovery before and after the intervention will be calculated and compared between the intervention and control groups using *t* tests if the data are normally distributed or the non-parametric Wilcoxon Rank Sum Test if the data are not normally distributed.

Secondary outcomes of interest include linear and ponderal growth, adverse gastrointestinal symptoms, and any side effects due to the interventions. Linear growth will be calculated as the change in length over time, expressed as mm/day. Weight change will be calculated as the change in weight over time, normalized to the enrollment weight, and expressed as g/kg/day. Exploratory analyses of mRNA markers of intestinal inflammation found in the stool will also be conducted as part of our ongoing investigations into identifying novel biomarkers for EED [43, 44].

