### Data management and analysis

Clinical data focusing on demographic and anthropometric values will be collected on standardized forms by field workers. Data will be double-entered into a password-protected Microsoft Access database by research assistants blinded to the intervention assignment. All discrepancies will be resolved by examination of the original forms and discussion with the relevant field workers. After entering all data and resolving inconsistencies, the data set will be locked. For anthropometric values, comparisons will be made between the lactoferrin-lysozyme mixture and the control rice flour groups. Fisher’s exact test will generally be used to compare discrete parameters, and Student’s *t* test will be used for continuous parameters. A difference with *P* < 0.05 will be considered statistically significant. These statistical methods will also be used for all clinical data and EED measures.

All trial data, including personal information, will be kept in password-protected encrypted computer databases on password-protected computers. Paper records will be kept in locked file cabinets and the research team’s headquarters in locked buildings. Given the relatively short duration of the study and the need to analyze all urine concentrations simultaneously at the end of the study, no interim analyses are planned and no stopping guidelines have been established. The full protocol, participant-level dataset, and details of all statistical analyses will be made available to any interested parties after the conclusion of the trial by contacting the principal investigators.

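### For a non-normal change in lactulose excretion, the protocol article prescribes two different primary tests: Wilcoxon in one section, Student's t test in another

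*Protocol article*

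**What the plan says.** The section Outcomes and sample size defines the primary outcome as "improvement of a major biomarker of EED", namely "the percent of ingested lactulose excreted in the urine (Δ%L), from baseline to 8 weeks and to 16 weeks". It then says how before-after differences in lactulose recovery will be compared between groups: by t tests for normal data, or "the non-parametric Wilcoxon Rank Sum Test if the data are not normally distributed". On sample size it states "This sample size was chosen to detect a decrease of 0.05% in Δ%L between the two groups", "with an alpha value of 5% and 90% power", with at least 86 children per group.

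The section Data management and analysis returns to testing. It begins with anthropometry, names Fisher's exact test for discrete variables, and says that Student's t "test will be used for continuous parameters". It sets no normality condition and closes the rule with "These statistical methods will also be used for all clinical data and EED measures". The significance threshold is P < 0.05.

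**The concern.** The lactulose measure is, by the protocol's own description, a biomarker of EED. It therefore falls under the general sentence as well as under its own specific rule. The two rules agree when the data are normal and part when they are not. An analyst facing a skewed or heavy-tailed change could run either test as primary and cite a section in support.

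Two things are at stake. The first is the error rate: two defensible P values for one primary comparison leave room to prefer the smaller. The second is what is being estimated. The trial is sized on a difference of 0.05 percentage points in mean change, and a rank sum test gives no estimate on that scale. With two primary time points, a data-driven switch could also yield a t test at 8 weeks and a rank test at 16 weeks, so the two primary results would not be on a common footing.

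**Working it through.** **Step 1. The two rules side by side.**

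| Change in %L | Outcomes and sample size | Data management and analysis |
|---|---|---|
| Normal | t test | Student's t test |
| Not normal | Wilcoxon rank sum | Student's t test |

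The rules conflict in the second row only. The adverb that softens the general rule is attached to Fisher's exact test, not to the t-test clause or the sentence on EED measures. The conflict is textual and depends on no figure. Steps 2 to 4 only size its consequence.

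**Step 2. The plan's own sample size.** Inputs from Outcomes and sample size: difference 0.05, alpha 5% (taken as two-sided, since sidedness is not stated), power 90%, 86 per group. No SD is given, so 86 cannot be reproduced directly. Solving n = 2·SD²·(1.960 + 1.282)²/0.05² for SD at n = 86:

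SD = 0.05 / (3.242 × √(2/86)) = 0.05 / (3.242 × 0.1525) = 0.101.

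A one-sided 5% test would imply 0.112. An SD of 0.10 returns 85 per group, so about 0.10 is the working value.

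**Step 3. What the choice of test does.** The documents give no distribution for %L, so shapes were assumed. There were 86 per group and 10,000 simulated trials per row. The assumed switch is Shapiro-Wilk at 5% in either arm. The design effect is 0.05/0.101 = 0.495 SD.

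| Assumed shape of the change | Type I: t | Type I: Wilcoxon | Type I: mechanical switch | Type I: more favourable test | Disagreement at design effect |
|---|---|---|---|---|---|
| Normal | 4.7% | 4.6% | 4.8% | 5.7% | 3.6% |
| t with 3 df | 4.9% | 5.3% | 5.4% | 7.2% | 9.0% |
| Difference of two log-normals | 5.0% | 5.1% | 5.1% | 7.3% | 9.7% |

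A separate simulation, with log-normal %L and SD of change 0.101, gave 4.7–4.8% for the mechanical switch, 6.3–6.9% for the more favourable test, and 6–10% disagreement at the design effect. In the two non-normal rows of the table, power is about 90% for the t test and about 99% for Wilcoxon.

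**Step 4. Naming a single analysis.**
- *t test:* 86 per group stands.
- *Wilcoxon with normal data:* matching the t test's power needs 86/0.955 = 90.05, so 91 per group.
- *Linear model adjusted for baseline %L:* with equal variances at both visits, the variance relative to the change score is (1 + ρ)/2, where ρ is the within-child correlation (not stated). At an assumed ρ = 0.3, SD = 0.101 × √0.65 = 0.0815. Then 0.05/(0.0815 × 0.1525) − 1.96 = 4.02 − 1.96 = 2.06, a power of about 98%. At ρ = 0.5, SD = 0.0876 and 3.74 − 1.96 = 1.78, about 96%. The log-normal simulation gave about 97%, against about 90% for the unadjusted t test, with type I error of 4.5–4.8%.

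**The case against.** The strongest reply is that the specific rule governs. Outcomes and sample size addresses the primary outcome by name, whereas the other section is a general summary that starts from anthropometry. On that reading nothing is open: the conditional rule was written in advance and, applied mechanically, holds type I error at about 5%. The protocol also keeps group information from those who analyse the data (Randomization and blinding) and plans a data lock and no interim analyses.

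Much of this stands. A reader might infer that the plan as written inflates type I error, or that its primary analysis is not pre-specified. The documents support neither. A stated conditional rule is pre-specified, and the 6–7.5% arises only if someone picks the better of two P values, which the plan nowhere prescribes. Nor is the missing normality criterion a defect in itself, since a statistical analysis plan may define it. Non-normality is plausible but not established: %L is bounded at zero, but its before-after change is not.

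A reader might also expect far more disagreement between the tests. A figure near 17% can be obtained with an assumed mean of 0.2, a coefficient of variation of 0.8 and a proportional effect. The SD of change is then about 0.19 and t-test power about 46%, which does not fit the stated 90%.

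What the reply does not remove is the contradiction. The document never says that the specific rule takes precedence, and the general sentence expressly reaches EED measures. A normality criterion in an analysis plan would leave the two sentences in conflict. Blinding does not settle which test is primary, because both P values can be computed from coded arms.

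**Conclusion.** The point holds as an inconsistency in the current text that should be corrected before the data set is locked. For a non-normal change in %L, the protocol article supports two different primary tests.

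The consequence is moderate: type I error of about 6–7.5% if the more favourable test is taken under skewed or heavy-tailed shapes, and about 5% if either test or a mechanical switch is followed. The tests disagree on significance in roughly 4–10% of trials at the design effect. These figures rest on an SD of change of about 0.10, back-solved from 86 per group at two-sided 5%, and on assumed distributions. The textual conflict rests on neither. Separately, if the rank test became primary, the main result would not estimate the 0.05-point difference used to size the trial.

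**What to change.** Name one primary analysis for %L at each of 8 and 16 weeks. The preferred choice is the between-group difference in mean %L from a linear model adjusted for baseline %L, with robust standard errors and a 95% CI. It estimates the quantity the trial is sized on and uses only data already collected. Replace the normality switch with this statement, and make the general sentence in Data management and analysis defer to it for the primary outcome. Report the Wilcoxon test as a sensitivity analysis. Naming either existing test and aligning the other sentence would be the minimum that removes the contradiction.

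The cost is two sentences of wording, with no added children or measurements. Recruitment was still under way at publication and all urine is to be assayed together at the end, so the choice could be fixed before outcome data exist. The small downside is that the rank test, which can be more powerful for strongly skewed changes (about 99% against about 90% for the t test and about 97% for the adjusted model, under the assumed shapes), is no longer available as primary.

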### Anthropometry

Anthropometric data will be obtained at every visit. Weight will be assessed to the nearest 5 g using standard digital scales (Seca 334, Chino, California, USA) and height will be measured to the nearest 0.1 cm using standard rigid height boards (Seca 417, Chino, California, USA). MUAC will be measured to the nearest 0.1 cm using standard flexible tape inserts (TALC, St. Albans, UK). Each child will be assessed for edema indicative of kwashiorkor by pressing on the dorsum of the left foot. The field research staff supervising anthropometry have been working in similar field sites and study conditions and trials for 5–15 years each, and will ensure that any junior research staff are fully trained and vetted prior to initiating the study. A random sampling of measurements each day will also be conducted by at least two field staff in order to verify that consistent and accurate measurements are being taken and corrective measures initiated as soon as any inaccuracies are identified.

Anthropometric *Z* scores will be calculated based on the 2006 World Health Organization (WHO) Multicentre Growth Reference Survey [50]. During both enrollment and subsequent visits, any child with a weight-for-height *Z* score less than –2, MUAC less than 12.5 cm, or presence of pitting edema will be classified as acutely malnourished and excluded from the study. Children excluded due to acute malnutrition will then be enrolled in supplementary or therapeutic feeding programs and receive usual medical care according to standard protocols [51–53].

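### The secondary growth outcomes are compared by an unadjusted t test across a 12–23 month age range, which is valid but gives up precision; the measurement is also called both length and height

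*Protocol article*

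**What the plan says.** All references are to the protocol article.

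- **Status.** Under Outcomes and sample size: "Secondary outcomes of interest include linear and ponderal growth".
- **Definitions.** The same section states: "Linear growth will be calculated as the change in length over time, expressed as mm/day". It adds: "Weight change will be calculated as the change in weight over time, normalized to the enrollment weight, and expressed as g/kg/day".
- **Comparison.** Data management and analysis states: "For anthropometric values, comparisons will be made between the lactoferrin-lysozyme mixture and the control rice flour groups". Student's t "test will be used for continuous parameters". No covariate is named, and the section extends these methods to all clinical data and EED measures.
- **Measurement.** Under Anthropometry, "height will be measured to the nearest 0.1 cm using standard rigid height boards". Lying or standing is not stated.
- **Z scores.** The same section says that anthropometric Z "scores will be calculated based on the 2006 World Health Organization (WHO) Multicentre Growth Reference Survey". The only use it states for them is the classification of acute malnutrition.
- **Age, follow-up and size.** Enrolment is at 12 to 23 months and treatment lasts 16 weeks. The target of at least 86 per arm was derived for urinary lactulose alone.

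**The concern.** Growth rate at this age can be expected to vary with the child's age, size and sex. A linear growth rate in mm/day takes no account of these, and a two-sample t test leaves whatever variance they explain in the error term. The randomisation list, as described, is not stratified by age, so chance age differences between the arms also remain in that error.

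Growth is secondary, but the study design section gives it as an aim alongside gut health, and the abstract makes linear growth the measure of stunting. The sample size gives no assurance of power for it. Removing explainable variance is therefore worth doing, and it needs no new data: age is needed for eligibility, weight and length are measured at every visit, and sex is needed for the Z scores.

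The second, smaller matter is terminology. The outcome is a change in length, but the measurement section describes height. A reader cannot tell from the article how the child is positioned, or that the position is fixed.

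**Working it through.** **The plan's own figure.** The article states no power or detectable difference for growth. The 86 per arm belongs to the lactulose outcome (difference 0.05, alpha 5%, power 90%). Its SD is not stated. Taking alpha as two-sided and solving back gives

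SD = 0.05 / [(1.960 + 1.282) × √(2/86)] = 0.05 / 0.494 = 0.101.

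This is the SD that makes 86 come out. It checks nothing about growth.

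**Detectable growth difference, unadjusted.** In SD units of the growth outcome, two-sided 5%, 86 per arm, normal approximation:

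- 90% power: (1.960 + 1.282) × √(2/86) = 3.242 × 0.1525 = 0.494 SD
- 80% power: (1.960 + 0.842) × √(2/86) = 2.802 × 0.1525 = 0.427 SD

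**With covariates.** If baseline value, age and sex together explain a share R² of the variance, the residual SD is multiplied by √(1 − R²), and so is the detectable difference. The article gives no R², so the range below is assumed. Example: R² = 0.10 gives √0.90 = 0.949 and 0.494 × 0.949 = 0.469 SD.

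| Assumed R² | Detectable at 90% power (SD) | Reduction | Power at 0.427 SD | Per-arm size giving the same precision unadjusted, 86/(1 − R²) |
|---|---|---|---|---|
| 0 | 0.494 | – | 80% | 86 |
| 0.02 | 0.489 | 1.0% | 81% | 87.8 |
| 0.05 | 0.482 | 2.5% | 82% | 90.5 |
| 0.10 | 0.469 | 5.1% | 84% | 95.6 |
| 0.20 | 0.442 | 10.6% | 88% | 107.5 |
| 0.30 | 0.414 | 16.3% | 92% | 122.9 |

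These figures ignore the small price of estimating three covariate effects. With N = 2 × 86 = 172, that price is a variance factor of about (N − 3)/(N − 3 − 3) = 169/166 = 1.018, or about 0.9% on the detectable difference. At R² = 0.02 it nearly cancels the gain; at 0.10 or more it matters little.

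**Length and height.** The two sections use different words for what must be the same measurement, since one board and one procedure are described for every visit. A change within a child is largely unaffected by posture if posture is constant. The article neither states that it is constant nor describes a change. No arithmetic applies here.

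**The case against.** **The t test is not an error.** With 1:1 randomisation it is valid and unbiased, the outcomes are secondary, and a growth velocity compared by t test is a defensible choice. All of this stands and limits the point to precision.

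**A fuller plan may name covariates.** An article often leaves adjustment to the statistical analysis plan, and this one says that details of all analyses will be made available after the trial. This stands in part. Silence would be no finding, but the article is not silent: it names the test for continuous measures. If a fuller plan already specifies an adjusted model, the point is met.

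**Z scores may already be covered.** The planned comparison of anthropometric values could include them. That reading is open, but they are not named as a growth outcome.

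**Stronger readings that the article does not support.**

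- A reader might infer from the two words, and from the fact that some children pass 24 months during follow-up, that children will be measured lying at first and standing later, producing a false drop in length. No section describes a second device, a change at a given age or mixed postures. Passing an age is not the same as being measured differently.
- A reader might call both growth outcomes raw. Weight change is not: it is "normalized to the enrollment weight, and expressed as g/kg/day". Size is therefore largely allowed for, though by a fixed proportional relation and without age or sex.
- A reader might conclude that mm/day and g/kg/day should be replaced. They need not be, since each can serve as the outcome of an adjusted model. With recruitment under way, demoting published outcomes would be a larger change than the problem calls for.

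**Conclusion.** The point holds as a modest gain in efficiency. The article specifies an unadjusted test where a model with the baseline value, age and sex would use data already available. The group comparison as planned is not biased. The loss is precision only, on secondary outcomes: about 1% to 16% of the detectable difference over an assumed R² of 0.02 to 0.30, with practically no net gain at the bottom of that range. The size rests wholly on that assumption, because the article gives neither a growth SD nor any relation of growth to age or size.

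The length/height wording is a minor ambiguity to tidy up. It is not evidence of measurement error, and no magnitude is claimed for it.

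**What to change.** 1. Before unblinding, specify that each growth outcome is compared between arms by a linear model with treatment, the baseline value of the measure (length for linear growth, weight for weight change), age at enrolment and sex. Keep mm/day and g/kg/day as the outcomes, so that the treatment difference stays in those units. Report the t test as a supporting analysis.
2. Use one term for the measurement in Outcomes and sample size and in Anthropometry, and state that the same posture is used at every visit for each child.

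**Cost.** No new data and no change to the outcomes. Because recruitment began in October 2016 and is continuing, the change to the analysis should be a dated, documented amendment or analysis-plan entry made while treatment assignment is still masked. The article plans no interim analyses and locks the data set after all data are entered and inconsistencies resolved, which leaves room for this. The second item is wording only, provided that it describes what the field staff already do.

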### Intervention groups

Following randomization, the experimental group will receive 1.5 g of bovine lactoferrin powder and 40 g of unpurified rice powder that contains 0.2 g of recombinant human lysozyme daily. The control group will receive 41.5 g of locally sourced rice powder daily. The amount of enzymes to be consumed per child per day is a conservative estimate based on the amount a typical breastfeeding 12-month old would receive daily and is consistent with previous studies [34, 45, 46]. Each group will receive their respective interventions for 16 weeks.

Bovine lactoferrin has been granted Generally Regarded as Safe (GRAS) status by the US Food and Drug Administration, and is widely used in studies of lactoferrin efficacy [23, 47, 48]. It will be acquired from FrieslandCampina (Amersfoort, Netherlands).

Bovine milk contains only trace amounts of lysozyme and is therefore not a viable source for this enzyme, but genetic modification has successfully integrated recombinant human lysozyme into rice. The transgenic rice has a normal plant phenotype; after harvest, the recombinant proteins are extracted and purified from milled rice powder as partially iron-saturated lysozyme [34]. The amino acid profile, iron content, peptide matching, chemical characterization, and functionality is identical to human lysozyme present in breast milk [49]. Ventria (Junction City, Kansas, USA) will be the supplier of the rice-based lysozyme product used in this study [34].

For the control group, a local variety of rice called faya will be used. It is an aromatic rice locally grown in Malawi with a nutritional profile similar to that used in the experimental formulation. The only processing this rice will undergo will be mechanical grinding; there will be no cooking, addition of chemicals, or other processes.

### Preparation of lactoferrin and lysozyme

Participants will receive their interventions packaged in clear plastic jars with adequate room for shaking and mixing, and will be instructed to store their interventions in a cool location with the caps screwed on tightly. Caregivers will be instructed to add the interventions to the child’s “phala”, which is the traditional morning dish of maize porridge that is commonly fed as the preferred complementary food. Phala is made by adding maize flour to boiling water and stirring over heat for about 15 min until thickened to the desired consistency. To avoid any denaturation or alteration of the interventions that may come with boiling, caregivers will be instructed to add the interventions after cooking is complete. Each participant will be given a small scoop with which to portion the correct amount of intervention, and they will be taught to mix the specified number of these scoops into the cooked phala. Acceptability tests in local children have shown that both the experimental and control interventions are palatable when mixed into this phala, with no adverse reactions noted.

